### Ethics

The study protocol has been reviewed and approved by the Ethical Review Committee of the Hainan Medical University. Ethical approval project identification code is 2018–4. The study will be carried out according to the principles of the Declaration of Helsinki. All participants will read the informed consent form, voluntarily agree to participate in this study and sign the informed consent form prior to the study. Written informed consent will be obtained from each participants before enrolment in the study, and then preserved by researchers.

### Study procedure

Participants will be followed throughout pregnancy to childbirth. And their infants will also be followed up to 42 days of age. Relevant indicators and outcomes will be measured and followed at the first trimester of pregnancy (15–17 weeks’ gestation), second trimester of pregnancy (20–22 weeks’ gestation), third trimester of pregnancy (30–32 weeks’ gestation), during childbirth and 42 days after childbirth (Fig. 1).

**Fig. 1 Fig1:**
[figure not shown]
Technology roadmap of study

After recruitment: Maternal socio-economics, socio-demographics and other basic information, such as pregnancy history, childbearing history, family history, disease history, drug use and anthropometric data of the participants will be collected after being recruited and entry into the study.

During the first trimester of pregnancy: Survey of fluid intake, dietary intake, psychological state, sleep quality and time, physical activities, history of disease and medication-use will be conducted using corresponding questionnaires at 1 weeks before antenatal care. On the day of antenatal care, anthropometric measurements, such as height, body weight and body composition, will be assessed by obstetricians. The first morning urine samples will be collected in sterile disposable urine sample cup and urine osmolality will be tested immediately by professional laboratory technicians. Antecubital venous blood will be collected to test hemoglobin, osmolality, hydration state regulating endocrine hormones – copeptin and pregnancy related endocrine hormones, including estradiol, prolactin, and progesterone. Pregnancy complications and other diseases or symptoms including urinary tract infection, anemia, edema and constipation will be assessed and diagnosed by obstetricians in accordance with the relevant physiological indicators. The occurrence time, duration and treatment measures of these outcomes will be recorded in detail as an important factor to be considered in later data analysis.

During the second and third trimester of pregnancy: the same procedure as the first trimester of pregnancy.

During childbirth and after childbirth: Before childbirth (One day before the expected date of delivery or one day before cesarean section), psychological state, sleep quality and time, physical activities and medication-use will be collected using corresponding questionnaires. On the day of childbirth, the mode of delivery will be recorded, pregnancy complications and other complications during childbirth will be assessed and diagnosed by professional obstetricians. Infant birth weight will be measured and health state will be assessed. Breastfeeding time and the crying behavior of infants before and after breast-feeding will be recorded. At 42 days after childbirth, maternal weight retention will be measured and calculated. Secretion of breast milk and mode of infant feeding will be consulted and infant growth will be assessed. Flow-process diagram of the study was shown in Fig. 2.

**Fig. 2 Fig2:**
[figure not shown]
Flow-process diagram of the study

If participants in this study requires hospitalization for any reason or receives intravenous fluid, or develops vomiting or diarrhea or fever or respiratory tract infections during pregnancy, the occurrence time, duration and treatment measures of these incidents will be recorded in detail. The time for recording fluid intake, food intake and other indicators will be exchanged within the allowable range of corresponding research phase to stagger the occurrence and duration of these situations.

The schedule of enrolment, data collections and assessments are shown in Table 2.

**Table 2 Tab2:** The schedule of enrolment, interventions, and assessments

Timepoint	15 April 2019	15 April 2019–30 September 2020	1 Octorber 2020
Enrolment:			
Eligibility screen	√	√	
Informed consent	√	√	
Collection of basic information	√	√	
Assessments of related indicators and outcomes during pregnancy and childbirth	√	√	
Close-out			√

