### Study design

A prospective observational cohort study is designed. A total of 380 pregnant women with < 13 weeks’ gestation will be recruited. All items from the World Health Organization Trial Registration Data Set are shown in Table 1.

**Table 1 Tab1:** Items from the World Health Organization Trial Registration Data Set

Data Category	Information
Registration number	ChiCTR1800019284, Chinese clinical trial registry
Registration State	1,008,001 Prospective registration
Public title	Study for the correlation between hydration state and pregnancy complications, maternal and infant outcomes during pregnancy
Scientific title	The correlation between hydration state and pregnancy complications, maternal and infant outcomes during pregnancy
Approval of ethic committee	Ethical Review Committee of the Hainan Medical University
Ethical approval project identification code	2018–4
Date of approved by ethic committee	20 May 2018
Study type	Prospective observational study
Study design	Prospective observational study
Key inclusion and exclusion criteria	Inclusion criteria: Aged between 21~35; at first trimester of pregnancy (before 13 weeks), in health state, without metabolic disease, oral diseases, and so on. Exclusion criteria: Aged < 21, or age > 35; not being at first trimester of pregnancy (before 13 weeks); With metabolic disease, oral diseases, and other diseases.
Outcomes	Urine and blood osomolality, fluid intake, copeptin, pregnancy complications, maternal and infant outcomes
Collecting samples	Urine and blood
Recruitment state	Not initiated
Randomization Procedure (please state who generates the random number sequence and by what method)	Not applicable. A convenience sampling method will be used to recriute participants.

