The most considerable challenges in this study is the following up of participants and quality control. Important protocol modifications will be discussed and determined by the researcher group, and will be communicated to investigators, trial participants and other relevant parties by e-mail immediately. In the study, participants will be followed up from the first trimester of pregnancy to 42 days after childbirth. To increase the rate of follow up, effective and convenient methods of communication between participants and researchers will be established, including telephone call, home visits, e-mail, WeChat, short message and so on. The content and purpose of the study will be clearly clarified to establish a relationship of trust and raise awareness of participants concerning the importance of the study. In this study, many methods will also be used to ensure the quality control. The requirements for participants will be fully explained. Participants will also be trained to be familiarized with the content of related questionnaires and study requirements. If a participant failed to follow the requirements, her data will not be included in this study and the reason for dropout will also be recorded. Researchers will be trained on the procedure of this trial, the content of the questionnaires and the technology-related laboratory tests. Some indicators such as height, weight, and blood pressure will be measured twice for accuracy, such as height, weight and blood pressure. Food models and photographic models will be provided to help participants fill the questionnaire related to food and fluid intake after training to enhance estimation accuracy. Physiological indexes, such as blood and urine indicators, will be tested immediately after collection, in order to ensure the accuracy, and will be tested by laboratory physicians with the minimum 5 years of clinical experience to ensure accuracy. Trial conduction will be audited by a competent authority in the hospital every day, and the process will be independent from investigators and the sponsor. All the questionnaires will be regularly checked and stored for researcher rechecks. A data monitoring committee (DMC) is established and is comprised by six members (three clinicians, one statistician, one ethicist and one nutritionists), who are independent of the sponsor and competing interests. DMC will review the procedure and data of the study for once a week. The six members will evaluate the safety concerns and benefits to decide that if the study should be continued or terminated. They will also examine the quality of the data, supervise the quality control, record the follow-up process and supervise the process of data entry and analysis. Four hydration and fluid intake related projects has been completed in China by our team; these provided an authoritative questionnaire and technical supports for the study.

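### As written, Table 2 runs screening and consent to the day before close-out, which does not fit entry before 13 weeks and follow-up to 42 days after childbirth

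*Protocol article*

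**What the plan says.** - **Calendar.** Table 2 (Study procedure) has three date columns: 15 April 2019, "15 April 2019–30 September 2020" and "1 Octorber 2020". The row "Eligibility screen" and the rows for consent and baseline information are ticked in the first two columns. So is the row for assessments in pregnancy and childbirth. Close-out alone is ticked in the third. The 42-day visit has no row of its own.
- **Entry.** Study design: "A total of 380 pregnant women with < 13 weeks’ gestation will be recruited".
- **Visits.** Study procedure places assessments at 15–17, 20–22 and 30–32 weeks, at childbirth and 42 days afterwards, and says of the offspring: "And their infants will also be followed up to 42 days of age".
- **End of follow-up.** The Discussion confirms that "participants will be followed up from the first trimester of pregnancy to 42 days after childbirth".
- **Loss allowed.** Sample size calculation allows 10% dropout and arrives at 380 women.

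The article gives no other date for the end of enrolment.

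**The concern.** A cohort that enters in early pregnancy and ends six weeks after birth needs a gap of many months between last entry and close-out. Table 2 leaves one day. Someone working from the table could go on consenting women who cannot reach delivery, or even a first assessment, before the study closes.

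The outcomes at stake are those seen only at or after birth: preterm birth, mode of delivery, gestational weight gain, postpartum weight retention, breastfeeding, birth weight and infant growth. They carry much of the third objective. Contact measures that improve retention cannot recover follow-up cut off by the calendar.

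**Working it through.** **Inputs from the article.** Screening and consent ticked from 15 April 2019 to 30 September 2020 (534 days elapsed, 535 counting both ends); close-out 1 October 2020; entry before 13 weeks, so at the latest 12 weeks 6 days (90 days); first assessment from 15 weeks (105 days); last visit 42 days after childbirth; preterm defined as below 37 weeks; 380 women; 10% dropout.

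**Assumptions.** The article gives no mean gestation at entry or delivery. I take entry at 8 weeks (56 days) to 12 weeks 6 days, and delivery at 37 weeks (259 days) to 40 weeks (280 days).

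**1. Can the stated close-out be reproduced?** A woman consented on 30 September 2020 at 12 weeks 6 days reaches 15 weeks after 105 − 90 = 15 days, on 15 October 2020. Even her first assessment falls after close-out, and a woman who enters earlier in pregnancy reaches it later still. No permitted gestation at entry makes the two dates agree.

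**2. Follow-up per woman** = (delivery day − entry day) + 42. The last entry that can complete is 30 September 2020 minus that number of days.

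| Entry | Delivery | Follow-up (days) | Last entry that can complete |
|---|---|---|---|
| 12w6d | 37 weeks | 259 − 90 + 42 = 211 (30w1d) | 3 March 2020 |
| 12w6d | 40 weeks | 280 − 90 + 42 = 232 (33w1d) | 11 February 2020 |
| 8 weeks | 37 weeks | 259 − 56 + 42 = 245 (35w0d) | 29 January 2020 |
| 8 weeks | 40 weeks | 280 − 56 + 42 = 266 (38w0d) | 8 January 2020 |

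Entry at 6 weeks with delivery at 42 weeks takes 42 weeks and moves the date back to 11 December 2019.

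**3. If enrolment did run to 30 September 2020.** Follow-up of the last woman would end between 29 April 2021 (211 days) and 23 June 2021 (266 days).

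**4. Share affected, if accrual were uniform over the 535 days** (the article gives no accrual rate). With delivery at 40 weeks:
- 42-day visit missed: 232/535 = 43% to 266/535 = 50%, or 165 to 189 of 380 women.
- Delivery at 40 weeks not yet reached: 190/535 = 36% to 224/535 = 42%.

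With delivery at 37 weeks and entry at 12 weeks 6 days, the first share falls to 211/535 = 39% (150 women). The plan allows 10%.

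**5. Direction of the truncation, if it occurred.** A woman entering at 12 weeks 6 days on 1 May 2020 would be at 90 + 152 = 242 days (34 weeks 4 days) on 30 September 2020. Her delivery would be on record by then only if it had already happened, that is, if it was preterm.

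**The case against.** The best defence is that the ticks are loose and the middle column is simply the overall study period. The row for assessments in pregnancy and childbirth is also ticked for the single day 15 April 2019, when no newly recruited woman could have had a 15-week or childbirth assessment. A tick may therefore mean only that an activity starts on, or falls within, a period. The column is shared by enrolment and follow-up, and about 17.5 months is long enough for both: on the working above, roughly 9 to 10.5 months remain for recruitment. A condensed article may leave the last-enrolment date to the full protocol, and the two flow figures are not shown in the text at hand.

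Much of this stands. The table does not prove that late enrolment was planned, and the overall dates need not change if recruitment stops early enough. It does not clear the table, though. Table 2 is presented as the enrolment schedule, it ticks screening and consent in a column ending the day before close-out, and nothing else in the article corrects it. This is a stated schedule that does not work, which is more than an omitted detail.

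Three stronger readings are tempting, and the article does not support them:
- **That the study will lose 43–50% of its 42-day data.** This needs enrolment to the tabulated date and uniform accrual. Neither is stated as a plan outside the table's ticks.
- **That preterm birth and low birth weight will be overstated.** This needs late enrolment, a close-out that acts as a hard data cut-off, and analysis of the truncated pregnancies. Close-out is not defined, and the text promises follow-up to day 42.
- **That nobody entering after January or February 2020 could finish.** Delivery at 37 weeks allows entry up to about 3 March 2020, and a preterm delivery later still.

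**Conclusion.** The concern holds as an inconsistency in the stated schedule. Screening and consent up to 30 September 2020 with close-out on 1 October 2020 cannot be reconciled with entry before 13 weeks and follow-up to 42 days after childbirth. That conclusion needs no assumption about accrual or time of delivery, because even the first assessment of a last-day recruit falls after close-out.

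The size of the gap does rest on assumptions. It is about 30 to 38 weeks for entry at 8 weeks to 12 weeks 6 days and delivery at 37 to 40 weeks. The lost share and any over-representation of early deliveries among late recruits are conditional consequences of following the table literally. They should not be reported as features of the design.

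**What to change.** Split the middle column of Table 2 into an enrolment period and a follow-up period, give the 42-day visit its own row, and choose one of two options:

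- **Keep close-out at 1 October 2020** and end enrolment about 38 weeks earlier, in early January 2020 or before. If entry before 8 weeks or delivery after 40 weeks is to be covered, December 2019 is safer. The cost is faster accrual: 380 women in about 8.8 months (15 April 2019 to 8 January 2020) is about 43 a month, against 380/17.5 = about 22 a month over the full window.
- **Define close-out as 42 days after the last enrolled woman's delivery.** If enrolment really runs to 30 September 2020, close-out moves about 7 to 9 months later, to between late April and late June 2021 on the assumptions above.

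If recruitment was always meant to stop earlier, the correction is one date in one table. No change to the analysis is needed once every woman can complete follow-up. Only if a fixed data cut-off that truncates follow-up is kept should delivery outcomes be restricted by due date, whatever the actual delivery date, so that early births are not selectively included.

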### Hydration related indicators and maternal-infant outcomes

Hydration related indicators and maternal-infant outcomes are summarized in Table 3.

**Table 3 Tab3:** Summarize of hydration related indicators and maternal-infant outcomes in this study

Related indicators and outcomes	Trimester of pregnancy			
	First trimester (15–17 weeks)	Second trimester (20–22 weeks)	Third trimester (30–32 weeks)	During and after childbirth
Related indicators				
Fluid intake	√	√	√	√
Dietary survey	√	√	√	√
Other influencing factors	√	√	√	√
Endocrine index	√	√	√	
Hydration state	√	√	√	√
Outcomes				
Physiological index	√	√	√	
Pregnancy complications	√	√	√	√
Other diseases or symptoms	√	√	√	√
Delivery mode				√
Maternal weight intention				√
Breast feeding				√
Infant weight				√

### Definition of hydration

Hydration state is determined by the balance between water inputs and outputs and judged by the standard of urine osmolality. Dehydration is judged as urine osmolality of > 800 mOsm/kg, and it occurs when water inputs is insufficient to replace water outputs [44]. Middle hydration state is judged as urine osmolality between 500 and 800 mOsm/kg [45]. Optimal hydration state is judged as urine osmolality of ≤500 mOsm/kg [45].

### Assessment of indicators and outcomes

#### Fluid intake

After standardized training by researchers, daily fluid intake of participants will be collected using a 7-day 24-h fluid intake record by themselves for correct use of such records. The amount of fluid intake for each time in seven consecutive days will be measured using a customized cup, and the nearest of cup scale is10 mL. This method has been proved to be reliable in many water intake-related studies [21, 46, 47]. The volume, type, time and place of water intake will also be recorded by participants. All types of fluid intake will be recorded in detail including plain water, bottled water, tea, sugar-sweetened beverages, and so on. The record will be photographed and sent by participants to the investigators using a mobile phone, and will be reviewed by investigators every day to ensure the accuracy and the integrity of the records.

#### Food intake and water intake from food

Food intake and water intake from food will be recorded and estimated using a semi-quantitative food frequency questionnaire (FFQ). The type, frequency and amount of food intake will be recorded. The amount of food intake will be estimated using by participants with the references of food models and photographic models [48]. Nutrients and water intake from food will be assessed by trained investigators using the *Chinese Food Composition Table* [49].

#### Psychological status:-anxiety and depression

Self-rated anxiety scale and self-rating depression scale will be used as indicators to assess the psychological status of participants [50–52]. Both scales, which mainly evaluates the frequency of symptoms, have 20 items each. Frequency will be rated on a 4-point scale: 1 indicates “never or seldom,” 2 indicates “sometimes,” 3 indicates “most of the time,” and 4 indicates “all the time”. For negative items, scores are graded sequentially according to the order from 1 to 4, and vice versa. The T score = total score for 20 items× 1.25 (the decimal portion is rounded). Standard of assessing anxiety: A T score 50–59 means mild anxiety, 60–69 means moderate anxiety, > 69 means severe anxiety, and < 50 means normal. Standard of assessing depression: T score 53–62 means mild anxiety, 63–72 means moderate anxiety, > 72 means severe anxiety, and < 53 means normal.

#### Sleep quality and time

The Pittsburgh Sleep Quality Index (PSQI) will be used to assess sleep quality and time for participants, which include 19 self-rating items and 5 others-rating items [53, 54]. Score is calculated including 19 self-rating items. Total 7 factors are measured in the 19 items: subjective sleep quality; sleep latency; sleep persistence; habitual sleep efficiency; sleep disorder; use of sleep drugs and daytime dysfunction. A 4-point scale is used, “0” means “no difficulty”; “2” means “moderate difficulty”; “3” means “severe difficulty”; and “1” means “mild difficulty”. The higher the score, the poorer the quality of sleep.

#### Physical activity

Information on physical activity will be collected by using the International Physical Activity Questionnaire (IPAQ) [55, 56]. The IPAQ consists of 27 items, incluing the type, frequency and duration of various physical activities. Participants will be classified into low-intensity, moderate-intensity and vigorous-intensity physical activity according to the similar criteria in some references [57, 58].

#### Anthropometric measurements

On the day of antenatal care, height and weight will be measured twice by professional obstetricians using the height-weight meter (HDM-300; Huaju, Yiwu, Zhejiang, China) following standardized processes to the nearest 0.1 cm and 0.1 kg, respectively. [BMI: weight (kg)/height squared (m)].

#### Indicators related to hydration state

About the evaluation criteria and indicators for hydration state, multiple indicators will be used for comprehensive evaluation, so body fluids, fluid intake, urine and blood osmolality are measured for evaluating hydration state in this study. At present, the internationally recognized and authoritative indicator is urine osmolality, which will be used as the primary determinant of the hydration state in this analysis of this study, and other indicators will be considered to be auxiliary indicators.

Intracellular fluid (ICF) and extracellular fluid (ECF): It will be measured by professional obstetricians using a body composition analyzer (Inbody 720; Inbody; Seoul, Korea) with the patients in a fasting state and after having defecated and urinated [59–61].

Urine and blood osmolality: The first morning urine samples will be collected in a sterile disposable urine sample cup, and blood will also be collected in vacuum tubes. Using an osmotic pressure molar concentration meter (SMC 30C; Tianhe, Tianjin, China) with the freezing-point method, osmolality will be determined by laboratory physicians, which will be used to assess the hydration state of participants.

Urine-specific gravity (USG): Using an automatic urinary sediment analyzer (FUS-200, Dirui, Changchun, China) with the uric dry-chemistry method, the first morning urine samples will be collected in sterile disposable urine sample cup to determine USG by laboratory physicians.

#### Endocrine indexes related to hydration and pregnancy

Copeptin as a hydration regulatory endocrine index and estradiol, prolactin, progesterone as pregnancy-related endocrine indexes will be tested in this study. The elbow venous blood will be collected in the morning and injected into a centrifugal tube containing 0.3 mol/L EDTA-Na2 and 5 × 10^5^ units of aprotinin. The supernatant was centrifuged at 3000 rpm/min for 15 min and stored at − 20 C. Then, these endocrine indexes will be determined with the method of radioimmunoassay with corresponding kits.

